### Secondary blood outcomes

#### Lipid profile

Fasting blood samples will be analyzed for the lipid profile (total cholesterol and fractions and triglycerides).

### Statistics

#### Sample size

The sample size was calculated from the literature [10, 12, 16, 17, 19, 23, 26, 27, 77] using the G*Power program (Heinrich-Heine-Universität Düsseldorf, Germany, version 3.1.9.6), inserting the parameters for a one-way ANOVA, effect size of 0.6 probability of error type alpha of 0.05 and power (probability of error type 1 –beta) of 0.9. With these parameters, 14 individuals will be needed (actual power of 0.93). Due to the usual sample loss of 25–40%, we will initially recruit 20 participants. In order to promote participant retention, frequent text messages will be sent as reminders to follow the instructions, and to show up in the scheduled sessions. Also, in case the participant misses a session, all effort will be made to reschedule as long as it is within 28 days of the previous session. Dropout reason will be recorded and reported in the manuscript.

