Data will be expressed as the mean and standard deviation with a confidence interval of 95%. For the analysis of data normality, we will perform the Shapiro-Wilk test. For normally distributed data, analysis of variance will be used with one source of variation (experimental situation). If a significant main effect was observed, post hoc Tukey test was used. For non-parametric data, the Kruskal-Wallis test was used, or Friedman’s test, when necessary. Effect size was calculated and interpreted as follows: <0.2 = no effect, 0.2–0.49 = low effect, 0.5–0.79 = medium effect, and greater than 0.8 = large effect [81, 82]. The significance level will be 5%. The Prisma program (GraphPad Software, San Diego, CA-USA–version 8.4.0) will be used to analyze the results. The trial will be reported following the CONSORT guidelines [83, 84].

As stated above under **Blinding procedures**, the researcher responsible for data analysis (the statistician) will be blinded for group allocation. For that, a collaborator outside the research team will double enter data coded for allocation into a computer in separate spreadsheets so that the researcher responsible for data analysis can assess data without having access to information about the allocation. Allocation will only be revealed after statistics are run. In case there are doubts about data entry (missing values, or values outside the reference range), the researcher responsible for data analysis will contact the collaborator outside the research team responsible for double entry of the data to check accuracy. There will be no interim analysis.

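### The sample-size statement of 14 individuals at power 0.93 does not follow from its stated parameters and is not the power of this three-session crossover or of its Tukey comparisons

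*Protocol article*

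**What the plan says.** In the Sample size section, the calculation is done in G*Power from a set of cited studies, "inserting the parameters for a one-way ANOVA, effect size of 0.6", with alpha 0.05 "and power (probability of error type 1 –beta) of 0.9". The result is "With these parameters, 14 individuals will be needed (actual power of 0.93". For attrition the section adds: "Due to the usual sample loss of 25–40%, we will initially recruit 20 participants". It gives no number of groups, within-person correlation, SD of differences or effect-size metric.

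Elsewhere the article describes a different structure from independent groups. Study type and design sets out a three-arm crossover in which every participant does the high-volume, low-volume and control sessions in random order. Data analysis plans an ANOVA with the experimental condition as its one source of variation, followed by Tukey comparisons if the main effect is significant. The same section gives a scale for interpreting effect sizes, on which "0.5–0.79 = medium effect, and greater than 0.8 = large effect".

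**The concern.** The text says that 14 people are needed under the listed parameters and that they give power 0.93. A reader should be able to reproduce this from the test named, and cannot. The nearest match under that test is 14 people in each of three independent groups, which is not the design.

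This is the trial's only stated sample-size justification, so readers will use it to judge what a null result means. The Discussion rests the clinical interest on whether low volume improves insulin action and how it compares with high volume. Those are pairwise questions, and 0.93 does not refer to them. A non-significant low-volume comparison could be read as evidence of no benefit on the strength of a power figure that was never calculated for it.

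**Working it through.** **Inputs from the Sample size section:** one-way ANOVA; effect size 0.6; alpha 0.05; target power 0.9; result 14 individuals, actual power 0.93. The number of conditions, k = 3, comes from Study type and design. The effect size is read as Cohen's f, the metric that G*Power takes for this test. The within-person correlation rho is not given, so it is an assumption, shown over a range.

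**1. The named test.** Power = P(F′ > F crit), where F′ is noncentral F with df (2, N − 3) and λ = f²N = 0.36N.

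| Total N | λ | df | Power |
|---|---|---|---|
| 14 | 5.04 | 2, 11 | 0.400 |
| 39 (13 per group) | 14.04 | 2, 36 | 0.906 |
| 42 (14 per group) | 15.12 | 2, 39 | 0.928 |

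The stated 0.93 appears at 42 people in total, not at 14. For a target of 0.9, the smallest balanced design is 39.

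**2. The design actually planned.** For 14 people measured under all three conditions, λ = f² × n × 3/(1 − rho) = 0.36 × 42/(1 − rho) = 15.12/(1 − rho), with df (2, 26).

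| rho | λ | Omnibus power |
|---|---|---|
| 0 | 15.12 | 0.917 |
| 0.5 | 30.24 | 0.998 |
| 0.7 | 50.40 | >0.999 |

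**3. What f = 0.6 means.** With three equally spaced means, the gap between the extremes is f√6 = 0.6 × 2.449 = 1.47 SD. With two equal means and one apart, it is 6f/√8 = 3.6/2.828 = 1.27 SD.

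**4. Tukey comparisons, 14 completers.** The critical |t| is 2.485 (studentized range for 3 means and 26 df, divided by √2). The noncentrality is d/√(2(1 − rho)/14). With f = 0.6 and equal spacing, adjacent conditions differ by 1.47/2 = 0.735 SD. At rho 0.5, for example, the noncentrality is 0.735/√(1/14) = 2.75.

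| Contrast (equal spacing) | rho 0 | rho 0.5 | rho 0.7 |
|---|---|---|---|
| Adjacent pair, e.g. low volume vs control (0.735 SD) | 0.31 | 0.61 | 0.85 |
| High volume vs control (1.47 SD) | 0.91 | 0.998 | >0.999 |

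If one condition instead stands apart from two equal ones, its contrasts (1.27 SD) have power 0.80, 0.985 and >0.999 at the same correlations. All these figures are for the comparison alone, without the added requirement of a significant main effect.

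**5. Caveat on the metric.** If 0.6 was meant as the standardised difference between the extreme conditions, f would be 0.6/√6 = 0.245 (equal spacing) to 0.6 × √8/6 = 0.283 (one apart). Omnibus power for the 14-person crossover would then be:

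| rho | 0 | 0.5 | 0.7 | 0.8 |
|---|---|---|---|---|
| Power | 0.25–0.32 | 0.46–0.58 | 0.69–0.81 | 0.86–0.94 |

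**The case against.** The strongest reply is that no harm to the omnibus test has been shown. Taken at face value as f, 0.6 gives the 14-person crossover at least 0.917 for any correlation of 0 or more, so 0.93 is about right or conservative. The 0.40 belongs to 14 people split over three parallel arms, which nobody proposes. This stands, and it limits the point: the statement is wrong as written, but the number of participants is not thereby shown to be too small.

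A reader might infer that a per-group figure was certainly mistaken for the total. The text does not prove this. A search for the smallest balanced one-way design would have stopped at 39 people with 0.906, not 42. A repeated-measures run at rho 0 returns exactly 14, at 0.917, which rounds to 0.92. Neither origin fits fully.

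A reader might also infer that 0.6 was a mean difference wrongly entered as f, and that the trial is badly underpowered. The only support is the interpretation scale in Data analysis, on which 0.6 would be medium. That scale is for reading observed results, not for the G*Power input, and the cited studies behind the 0.6 are not at hand.

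Finally, sizing on the omnibus test is consistent with a plan that goes to Tukey only after a significant main effect, and the Primary objective names no single contrast. The low pairwise figures apply to adjacent pairs under equal spacing; high volume versus control is well covered. What remains is that 0.93 says nothing about these comparisons.

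**Conclusion.** Wrong as written, and should be fixed; it is not a defect that invalidates the design. Under the named test, 14 people have power 0.40, and 0.928 needs 42. This rests only on k = 3 and on reading 0.6 as Cohen's f. For the crossover at the same f, omnibus power is 0.917 at rho 0 and 0.998 at rho 0.5, so the discrepancy is neutral to conservative for that test. Adjacent Tukey contrasts may be much weaker, at about 0.31 to 0.85 over assumed correlations of 0 to 0.7 with equal spacing. The low omnibus figures under a mean-difference reading of 0.6 are a reason to state the metric, not a finding that power is low.

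**What to change.** Keep the number of participants and delete the 0.93. Replace it with a calculation for the three-period within-subject design that:

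- states whether 0.6 is Cohen's f (1.27 to 1.47 SD between extreme conditions) or a standardised mean difference;
- gives the assumed within-person correlation, or the SD of within-person differences, with its source;
- reports the omnibus power for 14 completers;
- reports the Tukey-adjusted power, or the detectable difference, for each pairwise contrast with 14 completers.

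The cost is one recalculation and one rewritten paragraph, with no added participants and no change to conduct. The downside is that the stated power may look less favourable for some contrasts, notably those between adjacent conditions.

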#### Data analysis

To ensure confidentiality, all study-related information will be stored securely at the study site. All participant information will be stored in locked file cabinets in areas with access controlled by the principal investigator ([name]). All laboratory specimens, reports, data collection, process, and administrative forms will be identified by a coded ID number only to maintain participant confidentiality. All records that contain names or other personal identifiers, such as locator forms and informed consent forms, will be stored separately from study records identified by code number. No personal information from participants will be released outside the study. Full access to the complete dataset will be permitted only to [name] and to [name].

The statistical analysis will be conducted following the principles of intention-to-treat analysis [78]. Thus, data from subjects will be assessed as randomized, regardless of whether they received the randomized treatment, meaning that even if they fail to follow the physical activity and diet pre- and post-session instructions, or fail to complete the sessions as required (e.g. fail to achieve 9–10 in the OMNI scale), or fail to perform the OGTT at the schedule time, so-called non-adheres, their data will be included in the analyses. Furthermore, we will analyze the data “per protocol” [79], meaning that participants who deviate from instructions will be excluded from final analyses. Differences in results stemming from intention-to-treat and per protocol analyses will be discussed accordingly. The available variables will also be compared between participants who withdraw from the study and those who remain. Incomplete datasets (e.g., participant who complete 1 or 2 of the 3 sessions) will analyzed via sensitivity analysis of augmented data sets. Dropouts will be included in the analysis by modern imputation methods for missing data [80].

Data will be expressed as the mean and standard deviation with a confidence interval of 95%. For the analysis of data normality, we will perform the Shapiro-Wilk test. For normally distributed data, analysis of variance will be used with one source of variation (experimental situation). If a significant main effect was observed, post hoc Tukey test was used. For non-parametric data, the Kruskal-Wallis test was used, or Friedman’s test, when necessary. Effect size was calculated and interpreted as follows: <0.2 = no effect, 0.2–0.49 = low effect, 0.5–0.79 = medium effect, and greater than 0.8 = large effect [81, 82]. The significance level will be 5%. The Prisma program (GraphPad Software, San Diego, CA-USA–version 8.4.0) will be used to analyze the results. The trial will be reported following the CONSORT guidelines [83, 84].

As stated above under **Blinding procedures**, the researcher responsible for data analysis (the statistician) will be blinded for group allocation. For that, a collaborator outside the research team will double enter data coded for allocation into a computer in separate spreadsheets so that the researcher responsible for data analysis can assess data without having access to information about the allocation. Allocation will only be revealed after statistics are run. In case there are doubts about data entry (missing values, or values outside the reference range), the researcher responsible for data analysis will contact the collaborator outside the research team responsible for double entry of the data to check accuracy. There will be no interim analysis.

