### Dietary control

Participants will be instructed by a certified nutritionist on how to log their diet in a notebook on 3 nonconsecutive days of the week, one of the days being on the weekend [56]. Daily caloric intake in kilocalories (kcals) and kcals consumed from lipids, protein and carbohydrates will be analyzed using nutritional software (Dietbox Software, Brazil). Thereafter, a food plan will be given to the participants who will follow exactly the same food plan the day before and the day of the experimental sessions. This food plan will not change the composition and amounts of the daily basis food consumption of the participants, but they will be instructed to consume the same meals and the same amounts of food at the same hours of the day during the experimental protocol days, including a pre-session meal composed of 65% carbohydrates, 15% proteins, and 20% lipids one hour before reporting to the gym (~6:30 pm). Frequent text messages will be sent to participants to ensure they followed instructions. Adherence to dietary instructions will be verified by assessing their food record. After the experimental sessions, a standard snack (65% carbohydrates, 15% proteins, and 20% lipids) will be offered, which will be ingested between 9:00 and 9:30 pm at the gym where the sessions will take place, with calories determined from the individual daily needs, plus the estimated net energy expenditure of the session [57]. Participants will be instructed not to consume food after the offered snack and must fast until the morning of the next day to perform the OGTT in a local laboratory.

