#### Weaknesses

This study cannot be completed in a double-blind manner, as the participants and the researchers who will be present during the sessions will be aware of the treatment (high- or low-volume or control session). However, the professionals at the clinical lab who will collect and analyze the blood will be blinded to treatment, as well as the researcher who will perform the statistics. We will include obese men and women over 40 years old, so our results might not be readily translated to other clinical populations, such as younger, healthy individuals or individuals living with DM2. Furthermore, individuals with potentially different levels of insulin resistance might be included in this study, and greater exercise-induced improvement in insulin resistance has been observed in individuals with higher levels of baseline insulin resistance [26, 92]. Thus, this factor can also increase results variability. However, it should be pointed out that studying overweight/obese subjects regardless of their insulin resistance levels or fasting glucose impairment status is commonplace in the related literature [8, 93–95]. Nevertheless, the fact that participants will be their own control minimizes this potential source of variability. Moreover, individual results will be presented and discussed accordingly should individual levels of insulin resistance affect average group results. Furthermore, DM2 patients will be excluded, following our exclusion criteria. Also important to point out, participants might not follow the dietary and physical activity instructions the day before and the day of the sessions, which might also be confounding factors when interpreting our results. However, we will stress the importance of following these instructions by sending frequent text messages, and adherence will be verified when they report to the gym, and we will ask them to report what they ate to the nutritionist, which we believe increases adherence to diet prescription. Finally, per our study design, we will assess two significantly different strength exercise volumes, and by default time commitment, as lack of time is usually listed as one of the main reasons not to adhere to exercise [30]. Thus, our study design is not intended to explore a potential dose-response relationship between strength exercise volume and improvements in insulin sensitivity, although this approach would bear practical implications.

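### The intention-to-treat rule keeps OGTTs taken after a broken overnight fast as valid primary outcomes, which matters most for the fasting-based indexes (HOMA-IR, QUICKI)

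*Protocol article*

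**What the plan says.** **Fast.** Dietary control fixes a standard snack between 9:00 and 9:30 pm and then the fast: "Participants will be instructed not to consume food after the offered snack and must fast until the morning of the next day". Both are post-session diet instructions.

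**Outcome.** The section on primary blood outcomes calculates HOMA-IR and QUICKI from the minute-0 glucose and insulin, which it labels fasting values. It lists them with the OGTT-derived indexes as primary.

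**Intention-to-treat rule.** Data analysis lists the failures that do not remove data. Participants stay in "even if they fail to follow the physical activity and diet pre- and post-session instructions": "so-called non-adheres, their data will be included in the analyses".

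**Per-protocol rule.** The same paragraph adds a second analysis, "meaning that participants who deviate from instructions will be excluded from final analyses", and a commitment: "Differences in results stemming from intention-to-treat and per protocol analyses will be discussed accordingly".

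**Checks.** Dietary control verifies adherence from the food record. Weaknesses says that "adherence will be verified when they report to the gym" and adds a report to the nutritionist of what was eaten. The outcome section goes from arrival at the laboratory straight to the first blood draw.

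**The concern.** Intention-to-treat protects the comparison from selective exclusion of people who did not carry out the assigned session as planned. It does not make a failed measurement valid. Low effort in a set is non-adherence, and the OGTT that follows still measures what it should. A minute-0 sample drawn after eating does not measure fasting insulin or fasting glucose, so HOMA-IR and QUICKI calculated from it are not the quantities the protocol defines.

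The inclusion rule does not separate these cases. The per-protocol set does not separate them either: it drops the person, including the sessions with valid OGTTs, and does so equally for activity, effort, timing and diet. A reader is left with one analysis that contains the invalid value and another that discards much more than that value.

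In a sample of about 14, a single grossly raised fasting insulin can dominate the variance of a within-person difference. The only stated query of out-of-range values concerns data-entry accuracy, so a correctly entered unfasted value would pass.

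**Working it through.** **1. The plan's own figure.** Sample size gives a one-way ANOVA, effect size 0.6, alpha 0.05, 14 individuals, actual power 0.93. With 3 conditions and 14 observations in each, N = 42, noncentrality = 0.6² × 42 = 15.12, and the noncentral F on 2 and 39 df gives power 0.928. The stated figure reproduces.

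**2. Inputs the protocol does not give (assumptions).** HOMA-IR mean about 3, log-normal, between-person log SD 0.45; within-person CV 20%; true high-volume/control ratio 0.80; one of 14 high-volume values multiplied by 2.5 or by 4.

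**3. Effect on the mean.** In units of the control mean, one value inflated m-fold raises the high-volume mean by 0.80 × (m − 1)/14.
- m = 2.5: 0.80 × 1.5/14 = 0.086. The reduction shrinks from 20% to 11.4%.
- m = 4: 0.80 × 3/14 = 0.171. The reduction shrinks from 20% to 2.9%.

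**4. Power, paired t-test on HOMA-IR (20,000 simulated trials, n = 14).**

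| Data | Raw scale | Log scale |
|---|---|---|
| All values valid | 0.70 | 0.79 |
| One value × 2.5 | 0.13 | 0.26 |
| One value × 4 | 0.01 | 0.05 |
| That outcome set to missing (n = 13) | 0.66 | 0.75 |

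The pattern is the same at within-person CVs of 15% and 25%. Even a 1.5-fold inflation lowers raw-scale power to 0.50.

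**5. Power under the planned test sequence.** Data analysis plans Shapiro-Wilk, then ANOVA or a rank test, with Friedman's test named. Adding an assumed low-volume ratio of 0.90, repeated-measures ANOVA with a switch to Friedman on non-normality has power of about 0.62 with valid data and about 0.33 with one inflated value, at either 2.5 or 4 times. The outlier often triggers the rank test, which limits the damage but still costs nearly half the power.

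**6. HOMA-IR against Matsuda for the same broken fast.** Assume fasted values of 95 mg/dL and 12 µU/mL, and alter only minute 0.

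| Minute-0 glucose, insulin | HOMA-IR in that person | Mean HOMA-IR of 14 | Matsuda in that person | Mean Matsuda of 14 |
|---|---|---|---|---|
| 100, 18 | × 1.6 | +4.1% | −21% | −1.5% |
| 110, 30 | × 2.9 | +13.5% | −43% | −3.1% |
| 140, 70 | × 8.6 | +54.3% | −70% | −5.0% |

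The fasting product enters HOMA-IR directly but enters Matsuda under a square root. At an assumed between-person CV of 40–60%, the Matsuda shift is 21/60 to 70/40, about 0.4 to 1.8 SD. At the planned effect (f = 0.6, zero within-person correlation) that lowers power from 0.93 to no less than about 0.84. This last figure uses the plan's effect size, so it should not be set directly beside the powers in step 4. The percentage shifts of the mean are the like-for-like comparison.

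**The case against.** **Conventional pairing.** Keeping non-adherers in intention-to-treat, with a per-protocol analysis beside it and a discussion of differences, is usual practice and not an error. That stands. But the per-protocol set can remove only broken fasts that are detected, and it removes them together with that person's valid sessions.

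**The checks exist.** A reader might infer that nobody looks at diet after the gym. The documents do not support that: there is a food record and a nutritionist report. Neither is timed to the minute-0 sample. A fasting question at the laboratory is routine and may be in the full protocol, so its absence from a journal article is not itself the point. The point is the stated inclusion rule, which would keep the value even if such a check found a broken fast.

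**Worst-case arithmetic.** The inflation factors and CVs are assumptions, HOMA-IR is among the most sensitive of the listed indexes, and the protocol's Introduction itself calls it more limited than OGTT-derived ones. A rank test blunts an outlier. All of this stands and sets the limits of the conclusion.

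**Differential eating.** One might suppose that people eat more readily after 21 sets than after sitting still. No passage supports this, and the snack's calories already include the session's estimated energy expenditure.

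**Swapped sessions.** The phrase "data from subjects will be assessed as randomized, regardless of whether they received the randomized treatment" might be read as labelling sessions delivered in the wrong order by the envelope, which would reverse a crossover contrast. No passage says that would be done. The failures listed concern activity, diet, effort and timing, and the sessions are supervised.

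**Conclusion.** The point holds in a limited form. As written, the intention-to-treat rule admits an OGTT taken after a broken fast as a valid primary outcome, and no planned analysis removes only that measurement.

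For HOMA-IR under the assumptions shown, one such value inflated 2.5 times takes power from about 0.7 to 0.13 with a paired t-test, or from about 0.62 to 0.33 with the switch to Friedman. Treating the outcome as missing costs only a few points of power.

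A reader might infer that one unfasted sample cancels the trial's effect on every index. It does not. At the planned effect, the high-volume minus control difference is 1.27 to 1.47 SD, so cancelling it would take a shift of 14 × 1.27 = 18 to 14 × 1.47 = 21 SD in one value. Among the cases illustrated, only HOMA-IR after a recent meal approaches that; the Matsuda shift stays below 2 SD. The Matsuda figures assume that only minute 0 is disturbed. How often fasts would be broken is not known from the protocol.

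**What to change.** **Primary blood outcomes section.** State that the laboratory, still blinded, records the time of last food or caloric drink before the minute-0 sample, and that the OGTT is not run if the fast has been broken. The snack window is the same in all three sessions, so the answer does not reveal the condition.

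**Sample size section.** The existing provision, "all effort will be made to reschedule as long as it is within 28 days of the previous session", covers a missed session only. Extend it to a session whose OGTT could not be run, within the same 28-day limit, and say from which session the days are counted.

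**Data analysis section.** Take the broken fast out of the list of deviations whose data are included. An unfasted OGTT is a missing outcome for that session only, and the participant's other sessions stay in. Effort, activity and other diet deviations, including the snack, stay as assigned. The section already provides for incomplete datasets. Report the analysis with all OGTTs included as a sensitivity analysis.

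**Cost.** One recorded question per visit, a few sentences of text and an occasional repeated session. The drawback is that a few outcomes become missing, possibly in a way related to condition; the sensitivity analysis lets the reader judge whether that matters.

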#### High-volume session

All sessions will be held at the university facilities and will always be accompanied by the same certified fitness professional. Participants will report to the gym at 7:30 pm, where they will remain at rest until 8:00 pm, only receiving guidance on the exercises to be performed and will respond to the pre-session affection scale (see below in **Subjective measurements**), as suggested by Alves et al [58]. The experimental session will start at 8:00 pm and will be as follows: an initial 5 minute warm-up walking on a treadmill (~3–4 km/h) followed by 7 strength exercises that recruit the major muscle groups, performed in the order presented below: 1 –hex bar squat; 2 –bench press; 3 –leg press; 4 –lat pulldown; 5 –leg extension; 6 –shoulder press; 7 –leg curl. Participants will perform 3 sets with the previously determined 8-RM load, with as many reps per set as they tolerate (until concentric muscular failure–determined as the inability to maintain full range of motion or the inability to maintain tempo (~1:2 sec) for 2 consecutive reps, or by voluntary fatigue of the participant), with a rest of 120 s between sets and exercises. At the end of each set, they will respond to the OMNI-RES scale to ensure that they have reached maximum effort (9 or 10 on the scale). The number of reps performed in each set will be recorded to calculate the total exercise volume-load [59]. Based on pilot studies, sometimes the participant might not be able to complete the first rep of a given set, especially for latter exercises (e.g. leg extension and leg curl). In case that happens, we will not consider that set, will reduce the load by 5–10%, and give them 1 minute to rest after which another attempt will be made. If even after this the participant is unable to complete the first rep of the set, we will consider that the number of reps for that set was 0, and will move on to the next exercise, or finish the session (if this happens during the last exercise, e.g., leg curl). Also based on pilot studies, we anticipate this session will end between 8:45 and 8:55 pm. After that, participants will remain sedentary, answer the feeling, enjoyment, and self-efficacy scales (see below in **Subjective measurements**), and ingest the standard meal described above between 9:00 and 9:30 pm. After an overnight fast, they will report to a clinical analysis laboratory the next day in the morning (between 07:00 and 08:00 am) to perform the OGTT. Thus, the interval between the end of the session and the OGTT will be ~10 to 11 hours.

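### The per-protocol rule excludes participants although deviations occur by session, which can needlessly thin and select the low-volume versus control comparison

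*Protocol article*

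**What the plan says.** Under Data analysis, the protocol article makes intention-to-treat the leading principle: "The statistical analysis will be conducted following the principles of intention-to-treat analysis". It keeps non-adherers in that analysis: "so-called non-adheres, their data will be included in the analyses". The kinds of non-adherence it names are:

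- instructions on activity and diet: "even if they fail to follow the physical activity and diet pre- and post-session instructions";
- incomplete sessions, with effort as the example: "fail to complete the sessions as required (e.g. fail to achieve 9–10 in the OMNI scale";
- a glucose tolerance test not done at the scheduled time.

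A per-protocol analysis is then added, "meaning that participants who deviate from instructions will be excluded from final analyses". The plan also commits to interpreting the contrast between the two: "Differences in results stemming from intention-to-treat and per protocol analyses will be discussed accordingly".

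The effort check is described under High-volume session: "At the end of each set, they will respond to the OMNI-RES scale to ensure that they have reached maximum effort", with 9 or 10 as the target. The low-volume session follows the same procedures. Under Study type and design, the trial is a three-condition crossover with 21 sets in the high-volume session and 7 in the low-volume session. The control session has no repetitions.

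**The concern.** Each named deviation is an event of a single session, but the stated consequence falls on the person. In a crossover where everyone supplies three sessions, these units do not match. Someone who misses the effort target only in the high-volume session would also leave the low-volume versus control comparison, although both of those sessions were valid.

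That comparison carries much of the practical question in the Discussion, namely whether low-volume exercise by itself improves insulin action. Under the rule, its per-protocol estimate can depend on who tolerated a high-volume session that contributes no data to it. A reader told that the two analyses differ could not separate an effect of adherence from fewer pairs and a selected group.

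The same section handles a neighbouring case differently. A participant who attends only one or two sessions has those data used in a sensitivity analysis, whereas one who attends all three and deviates in one loses all three from the per-protocol analysis.

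**Working it through.** **Base number.** Sample size gives a one-way ANOVA, effect size 0.6, alpha 0.05, target power 0.9, 14 individuals and actual power 0.93. Taking 0.6 as Cohen's f with three groups of 14, the noncentrality is 0.6² × 42 = 15.12 with 2 and 39 degrees of freedom. Power is 0.928, so the stated figure reproduces. I use 14 people with all three sessions (42 sessions) as the starting point.

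**Equal deviation rates.** The document gives no rate. Assume each session deviates independently with probability p, and that one deviating session is enough to exclude.

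- Participant exclusion: pairs available for any contrast = 14 × (1 − p)³.
- Session exclusion: pairs available for a contrast = 14 × (1 − p)².

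| p per session | Participant exclusion | Session exclusion |
|---|---|---|
| 5% | 14 × 0.857 = 12.0 | 14 × 0.9025 = 12.6 |
| 10% | 14 × 0.729 = 10.2 | 14 × 0.81 = 11.3 |
| 20% | 14 × 0.512 = 7.2 | 14 × 0.64 = 9.0 |

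The ratio is 1/(1 − p). If the standard error goes with one over the square root of the number of pairs, participant exclusion widens it by √(1/0.9) = 1.05 at 10% and √(1/0.8) = 1.12 at 20%.

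**Effort failures only, low-volume versus control.** Equal rates are not what the design implies for effort. Assume each set misses the 9–10 target independently with probability q, and that any miss makes the session deviant. The control session cannot fail on effort.

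- Participant exclusion: 14 × (1 − q)²⁸, since 21 + 7 = 28 sets must all succeed.
- Session exclusion: 14 × (1 − q)⁷, since only the low-volume sets matter.

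| q per set | Participant exclusion | Session exclusion |
|---|---|---|
| 1% | 14 × 0.755 = 10.6 | 14 × 0.932 = 13.0 |
| 2% | 14 × 0.568 = 8.0 | 14 × 0.868 = 12.2 |
| 5% | 14 × 0.238 = 3.3 | 14 × 0.698 = 9.8 |

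The ratio is now 1/(1 − q)²¹, which comes entirely from the high-volume session.

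**Contrasts with the high-volume session, same assumptions.**

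- High versus low volume: 14 × (1 − q)²⁸ under both rules, so there is no gain.
- High volume versus control under session exclusion: 14 × (1 − q)²¹ = 11.3, 9.2 and 4.8 at 1%, 2% and 5%, against 10.6, 8.0 and 3.3 under participant exclusion.

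**Ordering of the two rules.** Anyone kept under participant exclusion has three valid sessions, and so has both sessions of every contrast. Session exclusion therefore never leaves fewer within-person pairs.

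**The case against.** The strongest reply has four parts.

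*The threshold is not stated.* The text does not say that one deviating session is enough, and operational detail of a per-protocol set is commonly left to an analysis plan. It is right that exclusion for a deviation in any session is an inference. But the unit of exclusion is stated, and someone who deviated once is, on the plain reading, a participant who deviated. If something else is meant, the sentence still needs changing.

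*The analysis is supplementary.* This stands. Intention-to-treat keeps every non-adherer, including those who miss the effort target.

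*Participant exclusion has a rationale.* It keeps the same people in all three conditions. Session exclusion could leave uneven numbers: on effort alone at 5% per set, about 4.8 high-volume, 9.8 low-volume and 14 control sessions. It also leaves contrasts with the high-volume session selected on tolerating that session. Both points stand as costs of the change, but neither justifies discarding a valid low-volume versus control pair.

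*The size is assumed.* A reader might infer that the per-protocol set will be very small, down to about 3 of 14. That needs a 5% miss rate per set, independent sets, and disqualification for a single rating below target. The document supports none of these, and it words the criterion by session. At 5% per session, 12.0 of 14 remain. Setting people kept under one rule against sessions kept under the other would also exaggerate the loss; pairs per contrast are the like-for-like unit.

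**Conclusion.** The point holds as a modest one that should be acted on. The stated rule excludes at the level of the person for events that occur at the level of the session, and on its plain reading it discards compliant sessions.

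Under equal assumed session rates of 5% to 20%, the avoidable loss is 0.6 to 1.8 pairs per contrast out of 14 (12.6 − 12.0; 9.0 − 7.2). For low-volume versus control it is larger if effort failures concentrate in the high-volume session: 2.4 pairs at 1% per set (13.0 − 10.6) and 4.2 at 2% (12.2 − 8.0). All rates, and independence, are assumptions.

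Two stronger readings are not supported. One is that the per-protocol set is simply selected on effort: diet, activity and test timing also count and can fail in any session, including control. The other is that differences between the two analyses would mainly be artefacts: without a documented deviation rate, one can say only that they could partly reflect lost precision and selection.

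**What to change.** Replace the per-protocol sentence with wording such as: in the per-protocol analysis the deviating session is excluded, not the participant, and the remaining sessions are analysed in a within-participant mixed model with condition as a fixed effect and participant as a random effect. Add that sessions are classified as compliant or deviating before allocation codes are opened, by a rule that says whether one set below the effort target is enough, and that the number of sessions excluded is reported by condition and reason.

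The cost is a few sentences and a model that accepts incomplete participants in place of a complete-block analysis. The downsides should be stated when results are reported:

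- contrasts will rest on partly different participants;
- retention may differ clearly by condition;
- a participant with one valid session adds nothing to a within-person contrast;
- selection in contrasts involving the high-volume session remains.
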